## Abstract

**Background:**

Increased appetite and weight gain are common adverse effects of glucocorticoid therapy in patients with systemic lupus erythematosus (SLE). Concerns about appearance-related changes due to weight gain can reduce medication adherence. Moreover, the complex interplay among glucocorticoids, mood changes, sleep disturbances, and appetite can influence eating behaviors. Daily data collection using ecological momentary assessment and analysis of interrelations may help clarify these dynamics. Furthermore, real-time feedback based on daily eating behavior may help patients regulate appetite and eating patterns. Accordingly, we developed Mogu!☆Log, a smartphone-based app that enables daily self-reporting of eating behaviors, appetite, and mood and provides graphical feedback on meal frequency and perceived control over eating.

**Objective:**

This paper presents a protocol for a pilot randomized controlled trial designed to evaluate the effects of real-time feedback on eating behaviors using the Mogu!☆Log app among patients with newly diagnosed SLE who had started glucocorticoid therapy.

**Methods:**

This multicenter study recruited Japanese patients with newly diagnosed SLE who had started glucocorticoid therapy across 15 hospitals with rheumatology services. Participants were randomly assigned in a 1:1 ratio to two groups: (1) the immediate feedback group, which receives graphical feedback on meal frequency and perceived control over eating starting from day 1, and (2) the delayed feedback group, which uses the same app without feedback for the first 14 days and begins receiving identical feedback from day 15. Participants enter data daily from day 1 to day 21 after randomization. The primary outcome is the mean number of meals on day 14 after glucocorticoid initiation. Secondary outcomes include the loss-of-control-over-eating score and a 5-item visual analog scale–based appetite score, both recorded on day 14. Between-group mean differences will be analyzed using 2-tailed *t* tests. The target sample size is 60. In an embedded observational “study within a trial,” linear mixed models will examine whether glucocorticoid dose influences appetite scores through mood and sleep changes.

**Results:**

We hypothesized that participants receiving immediate feedback will have fewer meals on day 14, reduced loss of control over eating, and better appetite scores. The study received funding in April 2019, April 2022, and April 2024. Recruitment began in October 2024, and 17 participants had been enrolled as of May 2025. Data collection is expected to be completed by March 2027; data analysis has yet to begin. Results will be submitted for publication and reported to the University Hospital Medical Information Network (UMIN) registry in the summer of 2027.

**Conclusions:**

This pilot trial will provide foundational data on the feasibility and efficacy of smartphone-based real-time feedback in managing glucocorticoid-induced appetite increase in patients with SLE. These findings may contribute to the growing body of literature on app-based interventions for medication-related adverse effects.

## Introduction

### Clinical Relevance of Glucocorticoid-Related Side Effects in Systemic Lupus Erythematosus

Glucocorticoids are the cornerstone of initial treatment for systemic lupus erythematosus (SLE), a disease that predominantly affects young to middle-aged women [1]. However, prolonged glucocorticoid use is associated with serious medical complications, such as infections and osteoporosis, as well as adverse quality-of-life effects, including increased appetite, weight gain, insomnia, and mood changes [2-4]. More than 30% of glucocorticoid users report experiencing weight gain and insomnia [5]. Furthermore, online patient communities frequently describe appetite increases and weight gain as distressing experiences [1]. Despite their prevalence, these side effects are often underrecognized in clinical practice and underexplored in research, with limited practical guidance available in standard medical literature.

### Unclear Mechanisms Underlying Glucocorticoid-Induced Appetite Changes

Prolonged glucocorticoid therapy induces weight gain [1], and patients with Cushing disease—characterized by chronic endogenous glucocorticoid exposure—commonly report increased food cravings rather than hunger [6]. Although exogenous glucocorticoid administration has been shown to increase food intake [7], the specific components of appetite affected by glucocorticoids remain unclear, possibly due to the limited use of validated appetite assessment scales in previous studies. Furthermore, the complex interplay among glucocorticoid use, mood changes, sleep disturbance, and appetite changes is poorly understood. Clinical glucocorticoid use is known to alter mood (eg, depression and irritability) and cognitive function (eg, difficulty with concentration and memory) [8]. Negative emotional states, in turn, can trigger increased food intake in healthy populations [9,10]. Whether similar mechanisms underlie glucocorticoid-induced appetite changes in patients with SLE remains uncertain. Although glucocorticoid-related sleep disturbances, such as insomnia, increased percentage of time spent awake, and increased percentage of time spent in slow-wave sleep, are well documented [11], it remains unclear whether these disturbances lead to mood deterioration similar to that observed in healthy individuals or those with mood disorders [12,13].

### Potential of Ecological Momentary Assessment and Feedback Interventions

Ecological momentary assessment (EMA) enables real-time monitoring of behavior and symptoms, offering a promising approach to clarify the dynamic interrelationships among appetite, mood, and sleep. In addition, behavioral interventions that incorporate daily feedback may help patients manage their appetite and eating behaviors. Smartphone apps delivering real-time feedback have shown potential in promoting dietary self-regulation among adults with obesity [14].

By using brief questions with simple response options and automated, immediate data processing [15,16], these tools minimize user burden and enhance sustained engagement through real-time feedback [14]. Consequently, such approaches may also benefit patients with SLE who experience appetite increases and weight gain following glucocorticoid therapy.

However, evidence regarding the use of EMA with real-time feedback in patients with glucocorticoid-treated SLE is limited. Although a previous study used an EMA-based smartphone app to assess meal frequency in healthy adults, most studies lack validated appetite measures or control groups [17]. Furthermore, existing EMA studies involving patients with SLE have primarily focused on sleep quality, without assessing appetite or mood [18].

### Development of a Smartphone-Based Monitoring and Feedback Tool

To address these gaps, we developed Mogu!☆Log (もぐ！☆ログ), a smartphone app designed to monitor and provide feedback on appetite, mood, and eating behavior. The app allows daily self-reporting and visual feedback and includes a built-in randomization function to assess the impact of feedback on behavior. By integrating clinical and sleep data, this tool facilitates a comprehensive EMA-based analysis of how glucocorticoid therapy influences appetite through mood- and sleep-related pathways.

### Objectives

This study aims to (1) evaluate the effect of real-time dietary feedback on meal frequency in patients newly diagnosed with SLE who have started with glucocorticoid therapy and (2) examine how glucocorticoids affect appetite through mood and sleep changes. We will conduct a pilot randomized controlled trial (RCT) to evaluate the feedback intervention, along with an embedded observational cohort study to explore interrelationships using multilevel modeling. This protocol is reported in accordance with the Standard Protocol Items: Recommendations for Interventional Trials (SPIRIT) guidelines [19] (Checklist 1).

## Methods

### Study Setting

This study is conducted in the rheumatology departments of 15 general or university hospitals in Japan, each comprising both outpatient and inpatient services. These hospitals were selected based on their established collaborative research relationships with the principal investigators (NK and NY) and their experience managing newly diagnosed patients with SLE.

### Eligibility Criteria

#### Inclusion Criteria

Inclusion criteria include patients who (1) are diagnosed with SLE based on the 1997 American College of Rheumatology classification criteria [20] and (2) have initiated glucocorticoid therapy for the first time, with dosage determined at the discretion of the treating physician. There are no age restrictions; however, as rheumatology departments primarily serve adult populations, the inclusion of minors is expected to be rare. Although SLE predominantly affects women, male patients are also eligible, and sex is not used as an inclusion criterion. Participants must be able to understand Japanese because the mobile app and all study materials are available only in Japanese.

#### Exclusion Criteria

Exclusion criteria include patients who (1) have neuropsychiatric lupus with seizures, confusion, disorientation, or delusions or (2) are unable to access the Mogu!☆Log app via the LINE platform (LY Corp).

### Intervention

Participants use Mogu!☆Log, a smartphone-based app delivered via the LINE platform, to record meal frequency and episodes of loss of control over eating. The intervention group receives real-time graphical feedback immediately after each entry, displaying data from up to the previous 7 days (Figure 1; English translation of the Japanese text displayed in the app is provided in Multimedia Appendix 1).

**Figure 1. F1:**
[figure not shown]
Feedback interface of the Mogu!☆Log smartphone app on the LINE social networking platform. (**A**) Graphical feedback showing self-evaluated eating episodes. Data from the past 7 days are plotted, with days on the x-axis and time (midnight to 11 PM) on the y-axis. Label size indicates perceived overeating (larger for episodes rated as overeating), whereas label color reflects perceived loss of control (red for loss of control, green otherwise). (**B**) Graphical feedback showing the frequency of eating episodes. Data from the past 14 days are presented, with dates on the x-axis and the number of episodes on the y-axis.

Two types of feedback are provided. The first graph summarizes eating episodes over the past 7 days, indicating whether overeating or loss of control occurred (Figure 1A). The second graph presents daily meal counts over the past 14 days (Figure 1B).

Participants register the day before glucocorticoid initiation and record data from treatment days 1 to 21 (Figure 2; English translation of the Japanese text displayed in the app is provided in Multimedia Appendix 1). Appetite and mood are assessed before and 2 hours after each meal. Overeating and loss of control are recorded immediately after every eating episode, including snacks. Before starting the study, participants received instructions on voluntarily logging entries before and after meals. The app automatically sends reminders for daily reporting. Reminders for postprandial entries (2 hours after a meal) were automatically scheduled based on each participant’s self-registered typical meal times (breakfast, lunch, and dinner). Specifically, these reminders were delivered randomly within +30 or −30 minutes of 2 hours after each registered mealtime (eg, if breakfast was set at 8 AM, the reminder was sent randomly between 9:30 and 10:30 AM). In addition, for immediate postmeal entries, if a participant did not submit an entry within 60 minutes after a premeal report, an automated reminder was sent.

**Figure 2. F2:**
[figure not shown]
Widget interface of the Mogu!☆Log smartphone app on the LINE social networking platform. (A) Main menu widget: clockwise from the top left—Appetite, Eating Behavior Evaluation, Log Review, User Settings, Morning/Night Entry, and Actigraphy Attachment. (B) Visual analog scale (VAS) input for appetite: users slide bars to rate hunger and satiety. (**C**) VAS input for eating episodes: users rate the degree of perceived overeating and loss of control during meals. (**D**) VAS input for mood: users rate depressed mood and irritation. Values for VAS inputs are automatically calculated based on the ratio of a slider’s position (distance from the left) to the full length between labeled end points.

The immediate feedback group receives graphical feedback from day 1, whereas the delayed feedback group does not receive feedback until day 14. After that, participants receive identical real-time feedback as the intervention group. The 14-day delay was determined for the following reasons: (1) at least 7 days of data are required to capture weekly behavioral patterns [15]; (2) a feedback duration longer than 1 week is desirable to detect behavioral change [17]; and (3) the accelerometer device used in the embedded “study within a trial” (SWAT) has a battery life of approximately 21 days, determining the total study duration. Accordingly, data collection spans 21 days, comprising a 14-day intervention or control phase followed by a 7-day delayed feedback phase, ensuring both groups eventually receive feedback exposure.

To encourage adherence, participants receive Amazon e-gift cards at registration and on days 7, 14, and 21 with the amounts corresponding to their logging activities.

### Outcome Measures

#### Primary Outcome

The primary outcome is the mean number of meals on day 14 after glucocorticoid initiation. This measure was selected to assess the impact of graphical feedback on eating behaviors. Meal frequency has previously been used as an index of the effectiveness of app-based feedback interventions [17].

Feasibility outcomes, including the completion rate and SD of the primary outcome, will also be reported to inform sample size estimation and refine the protocol for a future full-scale trial.

#### Secondary Outcomes

Secondary outcomes include loss of control before meals, loss of control during meals, and appetite, all assessed on day 14. Loss of control is measured using a visual analog scale (VAS) comprising 2 items: before meals, “To what extent do you feel in control of your eating?” (0‐100 scale); during meals, “During meals, how much did you feel out of control?” (0‐100 scale). Appetite is measured using a validated 5-item VAS-based scale for EMA [21].

We will also examine the 21-day trajectories of loss of control (ie, before and during meals) and appetite. Given the limited evidence on how glucocorticoid affects appetite over time, these trajectories will be analyzed separately for each feedback group.

#### Participant Timeline

Patients diagnosed with SLE and scheduled to begin glucocorticoid therapy are recruited 1 to 14 days before treatment initiation (Table 1). From days 1 to 21, all participants use the mobile app to report their mood, appetite, and eating behaviors. Participants also wear an actigraph continuously—except while bathing—to monitor their activity and sleep. Paper-based psychological and behavioral questionnaires are administered on days 1 and 21.

**Table 1. T1:** Participant timeline.

Time point in study timeline	Enrollment (day −14 to day −1)	Randomization (day 0)	Day 1 after randomization	Day 14 after randomization	Day 15 after randomization	Closeout (day 21)
Enrollment						
Eligibility assessment	✓					
Informed consent	✓					
Randomization		✓				
Intervention						
Immediate feedback			✓	✓	✓	✓
Delayed feedback					✓	✓
Assessment						
Baseline variables^a^	✓					
EMA^b^-based mood, appetite, and eating behavior^c^			✓	✓	✓	✓
Medication^d^			✓	✓	✓	✓
Actigraph-based physical activity and sleep data^e^			✓	✓	✓	✓
Paper-based questionnaire^f^			✓			✓

a Participant characteristics, including sex, birth date, age, psychiatric/psychosomatic outpatient status, height, weight, and disease activity (systemic lupus erythematosus disease activity index 2000).

b EMA: ecological momentary assessment.

c Sleep parameters, wake-up time, bedtime, mood (before sleep and before and after meals), appetite (before meals), perceived control over eating (before and after meals), and subjective assessment of meal quantity (after meals).

d Including glucocorticoids (prednisone-equivalent dose per day), psychotropic medications (hypnotics, antiepileptics, mood stabilizers, and antidepressants), hydroxychloroquine, and immunosuppressants.

e Including activity levels, nocturnal awakenings, wake after sleep onset, sleep onset latency, and sleep efficiency.

f A Three-Factor Eating Questionnaire-R18V2, Athens Insomnia Scale, Health-Related Hope Scale, and Short Grit Scale.

### Sample Size

The target sample size is 60 participants, taking into account the rarity of newly diagnosed SLE and the constraints of study duration and funding. This pilot trial aims to obtain key data for planning a future trial, ensuring at least 30 participants to estimate parameters for outcome measures (particularly SDs), as recommended in the pilot study design literature [22].

### Recruitment

Principal investigators (NK and NY) recruited rheumatologists from 15 hospitals across 5 Japanese regions (Hokkaido, Kanto, Chubu, Kinki, and Chugoku) through professional networks. Despite the rarity of SLE, recruitment was deemed feasible in both outpatient and inpatient hospital settings.

### Assignment of Interventions

The procedures for randomization and blinding are as follows:

Allocation—the app incorporates a simple randomization algorithm for participant assignment.Concealment—allocation is centrally randomized and concealed from both patients and physicians at enrollment.Implementation—physicians enroll patients, while the app performs group allocation automatically.Blinding—participants are blinded, although group inference may be possible based on feedback timing (health care providers remain blinded unless they view the participant’s screen; data analysts receive deidentified datasets without group assignment indicators).

### Data Collection and Management

Data were collected as follows: meal frequency was recorded electronically through user taps in the app at each eating occasion. VAS scores for loss of control, mood, and appetite were collected via in-app sliders with labeled anchors. Physical activity and sleep parameters, including activity levels, nocturnal awakenings, wake after sleep onset, sleep onset latency, and sleep efficiency, were measured using an actigraph (Table 1). These data were analyzed as outcomes or covariates in the SWAT.

Validated paper-based questionnaires included the Three-Factor Eating Questionnaire-R18V2 [23,24], Athens Insomnia Scale [25,26], Health-Related Hope Scale [27], and Short Grit Scale [28].

To promote retention, participants received Amazon e-gift cards on days 7, 14, and 21, with amounts proportional to the number of completed app entries.

Data management was conducted as follows: app data were securely transmitted and stored on an encrypted server. Input options were restricted to predefined ranges to ensure data validity. Paper-based data were double entered and cross-checked to identify discrepancies.

### Statistical Analysis

For the primary outcome, meal frequency on day 14 will be compared between groups using a 2-sided Student *t* test with a 5% significance level. For sensitivity analysis, an analysis of covariance will be performed, adjusting for disease activity and glucocorticoid dose.

For the secondary outcomes, between-group comparisons of loss-of-control and appetite scores on day 14 will be conducted using the 2-tailed Student *t* test. Sensitivity analyses with analysis of covariance adjusted for disease activity and glucocorticoid dose will be conducted. Longitudinal changes over the 21-day period will be analyzed using linear mixed-effects models with random intercepts for individual participants and fixed effects for group, time, and group-by-time interactions.

For the observational SWAT, linear mixed-effects models will be used to examine associations between glucocorticoid dose and outcomes such as appetite, snacking behavior, and loss of control. Mood and sleep variables will also be analyzed using the same modeling framework to assess the effect of glucocorticoid dosage. Additionally, linear mixed-effects models will be used to assess whether mood and sleep mediate the relationship between glucocorticoid dose and appetite. All models will incorporate random intercepts for individual participants and fixed effects for group, time, and group-by-time interactions.

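### The primary t test is unadjusted and the ANCOVA only a sensitivity analysis: with recruitment capped near 60, an ANCOVA on covariates fixed before feedback could give more precision at little cost

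*Protocol article*

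**What the plan says.** Statistical Analysis compares day-14 meal frequency between groups by a "2-sided Student *t* test with a 5% significance level". Adjustment is secondary: "For sensitivity analysis, an analysis of covariance will be performed, adjusting for disease activity and glucocorticoid dose". Loss of control and appetite on day 14 follow the same pattern: "Sensitivity analyses with analysis of covariance adjusted for disease activity and glucocorticoid dose will be conducted".

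Under Assignment of Interventions, "the app incorporates a simple randomization algorithm for participant assignment"; no stratification or blocking is described. The ratio is 1:1 (Abstract, Methods). Sample Size gives the reason for the target: "The target sample size is 60 participants, taking into account the rarity of newly diagnosed SLE and the constraints of study duration and funding".

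Table 1 lists the variables taken before randomization as "Participant characteristics, including sex, birth date, age, psychiatric/psychosomatic outpatient status, height, weight, and disease activity" (SLEDAI-2000). No eating frequency, appetite or control measure is among them. App entries start on day 1 (Intervention), when feedback also starts in the immediate group. Medication, including daily prednisone-equivalent dose, is ticked from day 1 after randomization onward.

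**The concern.** With about 30 patients per arm and nothing in the allocation to balance disease activity or dose, any outcome variation that these variables explain stays in the error term of the primary test. The number of patients cannot readily be raised, so covariate adjustment is one of the few remaining routes to a tighter estimate. The plan already specifies that adjustment but gives it the lesser role.

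Two details bear on how well it would work. Dose changes over the 21 days of recording, if it changes at all, come after randomization, so a day-14 or average dose would be a post-randomization covariate. And no scheduled measurement gives a clean baseline of the outcome, because on day 1 one arm already receives feedback. The pilot therefore cannot estimate the baseline-outcome correlation that a full-scale trial analyzed by ANCOVA would want for its sample size.

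**Working it through.** **The plan's own figure.** There is no power calculation to reproduce: Sample Size gives no effect size, SD, power or dropout. Results below are in units of the unknown outcome SD.

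**Inputs from the article.** N = 60, taken as 30 per arm; two-sided 5% test; two ANCOVA covariates (disease activity, dose). **Assumption.** R, the multiple correlation of the covariates with day-14 meals, is varied from 0 to 0.5.

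**Step 1: unadjusted reference.** The standard error is sqrt(2/30) = 0.258 SD. The 95% confidence interval half-width is 2.002 × 0.258 = 0.517 SD. The minimum detectable difference at 80% power (noncentral t, 58 df) is 0.736 SD.

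**Step 2: ANCOVA relative to the t test.** With k covariates, the expected ratio of standard errors is sqrt[(1 − R²) × (1 + k/(N − k − 3))]. The second factor is the cost of estimating the covariate slopes. Equivalent unadjusted N is 60 divided by the squared ratio. For k = 2 the cost factor is 1 + 2/55 = 1.0364.

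| R (assumed) | Squared ratio | SE ratio | Equivalent N | Detectable difference | Power at 0.736 SD |
|---|---|---|---|---|---|
| 0 | 1.000 × 1.0364 = 1.036 | 1.018 | 58 | 0.749 SD | 78.5% |
| 0.2 | 0.960 × 1.0364 = 0.995 | 0.997 | 60 | 0.734 SD | 80.1% |
| 0.3 | 0.910 × 1.0364 = 0.943 | 0.971 | 64 | 0.715 SD | 82.2% |
| 0.5 | 0.750 × 1.0364 = 0.777 | 0.882 | 77 | 0.649 SD | 88.8% |

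Break-even: R² = 1 − 1/1.0364 = 0.035, so R is about 0.19.

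**Step 3: a pre-randomization meal count.** Used alone (k = 1, cost factor 1 + 1/56 = 1.018) and available for everyone, it would give an equivalent N of 65, 79 and 116 at R = 0.3, 0.5 and 0.7. It would not be available for everyone: 17 had been enrolled by May 2025, and 17/60 = 28%. Two existing covariates, the count and a missing indicator make k = 4, with cost factor 1 + 4/53 = 1.075. Equivalent N is then 60/1.075 = 56 at R = 0, 60/(0.91 × 1.075) = 61 at R = 0.3 and 60/(0.75 × 1.075) = 74 at R = 0.5. Break-even rises to R of about 0.26.

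**Step 4: simple randomization by itself.** Under Binomial(60, 0.5), unequal arm sizes inflate the variance by 1.8% on average. A split of 24:36 or worse has probability 15.5%, and at 24:36 the standard error is 2.1% larger. This is a small cost.

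**The case against.** The strongest reply is that nothing here is wrong. An unadjusted t test is valid after simple randomization, the ANCOVA is already planned for primary and secondary outcomes, limited power is acknowledged under Limitations, and the pilot was not sized for power. All of that stands. The SD to be reported as a feasibility outcome is also unaffected: chance imbalance between arms does not bias a pooled within-arm SD.

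Several stronger readings are tempting, and the article does not support them:

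- *That 60 patients would become 80.* This takes R = 0.5 and only the factor 1 − R² (60/0.75 = 80). The article gives no correlation, and slope estimation has a cost. Naming dose and disease activity as covariates does not show how strongly they predict meals; the Introduction calls the effects of glucocorticoids on components of appetite unclear.
- *That chance imbalance is a further problem.* With 30 per arm, a covariate differs by more than 0.3 SD with probability of about 25%. At a correlation of 0.5 that moves the raw difference by at least 0.15 SD. But 0.15/0.258 is about 0.6 standard errors, and this variation is already inside the t test's standard error.
- *That inpatient status must be adjusted for.* Recruitment says that "recruitment was deemed feasible in both outpatient and inpatient hospital settings", but that setting drives meal count is an outside assumption. The baseline list is also worded as non-exhaustive.
- *That the dose covariate is misused.* The article does not name the day, and a separate analysis plan may. Nothing in the article suggests that feedback alters dose. The point is only to rule out a later dose if the ANCOVA becomes primary.
- *That the whole remedy is free.* That is nearly so for the planned covariates. A baseline meal count needs new data.

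**Conclusion.** The point holds as an efficiency improvement. The primary test is valid but unadjusted, and the adjusted analysis already in the plan could serve better as primary. With the two existing covariates, the effect ranges from a standard error about 2% larger (R = 0) to about 12% smaller (R = 0.5), with no net gain below R of about 0.19. This rests on an assumed R, arms of about 30, and covariates fixed before feedback can act. The loss is possible and not demonstrated. The change is still worth making, because its downside is small and bounded and recruitment cannot easily make up the precision.

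**What to change.** Before analysis begins (the article reports that it had not):

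1. Name the ANCOVA as the primary analysis of day-14 meal frequency and the t test as its sensitivity analysis. Do the same for loss of control and appetite.
2. Define the covariates as SLEDAI-2K at enrollment and the glucocorticoid dose at initiation (day 1). State that a day-14 or average dose will not be used.
3. Optionally, for remaining participants, add one registration question, answered before the app randomizes, on the usual number of eating occasions per day including snacks. Use it as a covariate, with the missing-indicator method for those already enrolled, and report its correlation with day-14 meals for planning the full trial.

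Items 1 and 2 cost wording and two degrees of freedom, with a standard error up to about 2% larger if the covariates are not prognostic. Item 3 costs a small change to a live app that also randomizes, an amendment across 15 hospitals, and further degrees of freedom. Its gain is diluted because the covariate is missing for at least 17 of 60.

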### Advantages and Challenges of Real-Time Graphical Feedback

Advances in mobile health technologies have heightened interest in app-based self-monitoring and feedback interventions. For patients starting glucocorticoid therapy, monitoring appetite and eating behaviors may help mitigate glucocorticoid-induced hyperphagia. However, the burden of frequent data entry may reduce adherence, and interventions lacking validation should be applied with caution. A previous study in the general population reported that dietary logging apps reduced meal frequency and prolonged intervals between meals [17]; however, its single-arm, pretest-posttest design limited causal inference. To address this limitation, this study compares immediate and delayed (2-week) graphical feedback, allowing for direct evaluation of the specific impact of real-time feedback on eating behavior. Furthermore, examining changes in eating behavior between days 14 and 21 in the delayed feedback group—after feedback is introduced—may further clarify the behavioral impact of this intervention.

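### The 21-day longitudinal model has no term for the control arm's switch to feedback on day 15, so its group-by-time effect need not measure feedback versus no feedback

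*Protocol article*

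**What the plan says.** All references are to the protocol article.

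- **Model.** Statistical Analysis, for the secondary outcomes: "Longitudinal changes over the 21-day period will be analyzed using linear mixed-effects models with random intercepts for individual participants", with "fixed effects for group, time, and group-by-time interactions". No phase or exposure term is named, and the section does not say whether time is linear or coded by day. It gives the same fixed effects to all models of the embedded observational study.
- **Exposure.** The Abstract (Methods) says that the delayed arm "uses the same app without feedback for the first 14 days and begins receiving identical feedback from day 15". Table 1 also marks delayed feedback from day 15. The Intervention section says "the delayed feedback group does not receive feedback until day 14" and then "After that, participants receive identical real-time feedback as the intervention group". It describes the 21 days as "comprising a 14-day intervention or control phase followed by a 7-day delayed feedback phase".
- **Trajectories.** Secondary Outcomes says of the 21-day courses of loss of control and appetite that "these trajectories will be analyzed separately for each feedback group".
- **Use of the last week.** The Discussion suggests that "examining changes in eating behavior between days 14 and 21 in the delayed feedback group" may help to clarify the effect of feedback.
- **Between-group tests.** The *t* tests and analyses of covariance for the primary and secondary outcomes are at day 14.

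**The concern.** The design has two regimes: 14 days of feedback against none, then 7 days with feedback in both arms. The stated model treats the 21 days as one. If feedback works, the arms should separate and then draw together once the control arm receives it. A single linear group-by-time slope cannot follow that path. It averages the separation and the convergence, so an intervention that works could show a weak slope or one in the wrong direction.

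The text also describes the trajectory analysis in two ways. Analysis separately by group gives no between-group test, whereas the joint model with an interaction does. If the delayed arm's last week were read without the immediate arm's concurrent change, any effect of feedback would be mixed with time on glucocorticoids. Secondary Outcomes says that evidence on this time course is limited.

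At stake is the supporting longitudinal analysis of loss of control and appetite, which is where the daily data are used.

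**Working it through.** **No figure to reproduce.** The article attaches no effect size, SD or power to this model. Its one piece of arithmetic, 14 + 7 = 21 days, is right, and 7/21 = 33% of the window has both arms on feedback.

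**Method.** With complete, balanced data, random intercepts and linear time, the group-by-time coefficient equals the least-squares slope of the between-arm mean difference D(t) on day t:

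slope = Σ(t − t̄)·D(t) / Σ(t − t̄)²

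- Days 1-21: t̄ = 11, denominator 770.
- Days 1-14: t̄ = 7.5, denominator 227.5.

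Let f(d) be the effect after d days of feedback. Then D(t) = −[f(t) − f(t − 14)], with f = 0 for d ≤ 0. The fitted day-14 difference is mean(D) + slope × (14 − 11).

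**Assumptions.** The onset shape f and the maximum effect of −1 are assumed; the article gives neither. A ramp of length L means f(d) = min(d/L, 1).

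**Immediate effect.** D = −1 on days 1-14 and 0 on days 15-21.
- Σ(t − 11)·D = 49, so the slope is 49/770 = +0.064 per day. Over days 1-14 it is 0.
- Mean difference: −14/21 = −0.67, against −1.00 over days 1-14.
- Fitted day-14 difference: −0.667 + 3 × 0.0636 = −0.48, against a true −1.00.

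**5-day ramp.**
- Days 1-21: numerator 22 (days 1-5) + 9 (days 6-14) − 10 (days 15-18) = 21; slope 21/770 = +0.027.
- Days 1-14: numerator 11.5 − 22.5 = −11; slope −11/227.5 = −0.048.

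**14-day ramp.**
- Days 1-21: numerator 10 (days 1-14) − 33 (days 15-21) = −23; slope −23/770 = −0.030.
- Days 1-14: slope −1/14 = −0.071. The 21-day slope keeps 42% of it.

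| Assumed onset | Slope, days 1-14 | Slope, days 1-21 | Fitted day-14 difference (true −1.00) |
|---|---|---|---|
| Immediate | 0.000 | +0.064 | −0.48 |
| 3-day ramp | −0.027 | +0.045 | −0.53 |
| 5-day ramp | −0.048 | +0.027 | −0.58 |
| 7-day ramp | −0.064 | +0.009 | −0.64 |
| 10-day ramp | −0.076 | −0.014 | −0.69 |
| 14-day ramp | −0.071 | −0.030 | −0.68 |

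**Sensitivity to the day origin.** If the ramp starts one day later in both arms, the 3- and 5-day ramps still reverse. The 7-day ramp does not: it gives −0.009 against −0.079, about 12% retained.

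**Sensitivity to shape.** For an effect that is greatest on day 1 and wanes with a 7-day half-life, the slope goes from +0.054 to +0.086, neither attenuated nor reversed. The mean difference still shrinks, from −0.57 to −0.19.

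**Time coded by day.** Mixed models were simulated with 30 per arm and assumed SDs of 0.7 between persons and 0.8 residual. Over four shapes, with 10 runs each, the average day-14 contrast was −0.95 to −1.11, near the true −1. Contrasts up to day 14 are therefore not distorted.

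**The case against.** The strongest reply is that the article does not say time is linear. The plural in "fixed effects for group, time, and group-by-time interactions" is compatible with time coded by day, and a condensed article may leave that coding to the full plan. This stands: the slopes above are conditional on linear time. It does not remove the point. The window and the fixed effects are fixed in the text without the switch, no contrast is named, and an overall interaction test with day-by-day coding would still pool days 15-21.

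Second, the article never calls this coefficient the treatment effect. It places the between-group comparison at day 14, and the reason it gives for studying trajectories is the little-known time course of glucocorticoid effects on appetite. That also stands, and it limits the importance of the point. Still, a joint model with a group-by-time term invites a between-group reading.

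Third, a reader might infer from the Discussion that the delayed arm's last week will be analysed alone, as an uncontrolled before-after comparison. The text does not go that far. The remark is hedged, follows the randomized comparison and specifies no analysis. It only shows that a comparator for those days should be named if they are used.

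Fourth, the onset shapes are assumed, and the sign change at seven days depends on the day origin. This is correct, so reversal is a possibility under fast onset and not a prediction.

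**Conclusion.** The point holds in limited form. The longitudinal model for loss of control and appetite crosses the day-15 switch with no term for it. With linear time, its interaction does not estimate feedback versus no feedback. For the assumed effects complete by day 14, the coefficient is attenuated, reversed or spurious, and the fitted day-14 difference is about −0.5 to −0.7 where the truth is −1.

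A reader might infer that the trial's treatment effect will be attenuated or reversed. The document does not support that. The coding of time is open, the size and sign depend on an onset shape that nobody has specified, and the day-14 primary and secondary comparisons precede the switch and are untouched. So are the feasibility outcomes. This is a should-fix for a supporting analysis in a pilot.

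**What to change.** 1. Estimate the randomized between-group effect from days 1-14. Alternatively, keep all 21 days and add a day-15 phase term or a time-varying feedback-on indicator. State how time is coded and name the contrast of interest.
2. If days 15-21 are used to judge the delayed arm's response, compare its change with the immediate arm's change over the same days.
3. Reconcile Secondary Outcomes with Statistical Analysis: keep separate-by-group trajectories as description and the joint model for inference.
4. Reconcile the Intervention wording on when delayed feedback begins with the Abstract and Table 1, so that the phase boundary is unambiguous.
5. Check whether the observational models, which carry the same fixed effects, also need the phase or exposure term.

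The cost is a few sentences and a few lines of model code. No data collection changes, and the article says that analysis has not begun.
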